**Fig. 1 Fig1:**
[figure not shown]
Flow diagram

### Inclusion criteria

Stratum I (nonoperative treatment vs. ORIF):Non-dislocated (< 2 mm) fractures affecting TMT joints II and IIIAnd/or Dislocation < 5 mm between medial cuneiform and base of MT IIAnd no fractures affecting TMT joints IV and V

Stratum 2 (ORIF vs. PA):Affected joints TMT II - III + any other TMTAny dislocation > 2 mm (fracture or TMT joint)Dislocation > 5 mm between medial cuneiform and base of MT II

### Exclusion criteria

Aged under 18 or over 60Open fracturesExtra-articular metatarsal fracturesExtremely comminuted fractures with bone loss and poor chance of gaining proper fixation with screwsPolytrauma patientsPatients with weak co-operation (dementia, alcohol use, etc.)Patients with significant neuropathy or some other neurological conditionDiabetesRheumatoid arthritisPatients with severe circulatory disorder of the lower limbA delay in diagnosis of more than 14 daysPatients with a previous foot injury or surgery of the injured footPregnancyPatients who refuse to participate

### Randomization

All patients will be randomized by the research coordinator at Tampere University Hospital who will not participate in the study. Patients with non-dislocated injuries are randomized into a nonoperative or ORIF group. Patients with dislocated injuries will be randomized into ORIF or PA groups. Both injury types will be randomized in blocks of ten. The treatment allocations from the randomization will be sealed in envelopes which will be then used and opened in numerical order after patient enrolment has been confirmed by the research physician. The research coordinator will monitor the study flow.

### Nonoperative treatment

Nonoperative treatment is conducted with non-weight-bearing cast-immobilization for 6 weeks. The cast is changed at 1 and 2 week controls. The cast is removed at 6 weeks and patients are prescribed a walking boot for 4 weeks. Weight-bearing with a walking boot is limited to half-bodyweight for the first 2 weeks and the last 2 weeks as tolerated. At 10 weeks, patients will be allowed to use their own shoes and walk as tolerated.

### Open reduction and internal fixation

One or two incisions will be made depending on the location of the injury. Only the affected and instable TMT joints are fixed. The first incision is made between MT I-II and the second incision (if necessary) at the base of MT IV. Open anatomical reduction and screw fixation of the 2nd metatarsal to the medial cuneiform bone (‘home run screw’) and affected TMT joints will be performed with 4.0 cannulated screws (DePuySynthes©, Stryker©). If TMT IV or V joints are dislocated, after open reduction of those joints, temporary fixation with Kirschner-wires will be used (Fig. 2). Fixation will be performed under fluoroscopic guidance. K-wires will be cut, bent and left visible on the skin and removed at the 6 week postoperative visit. Wounds will be closed with dermal sutures. Fixation screws will be removed only if they cause any symptoms.

**Fig. 2 Fig2:**
[figure not shown]
Intraoperative view of the screw and K-wire fixation of the TMT joints

### Primary arthrodesis

Incisions will be made as described for ORIF. Cartilage and fibrous tissue will be removed from the affected TMT joints with a chisel. Fixation for the medial cuneiform bone to the base of 2nd metatarsal and TMT I-III will be performed with 4.0 cannulated screws in a similar manner to ORIF. If TMT IV or V joints are affected, arthrodesis will not be done, but temporary fixation will be performed, as described for ORIF.

### Postoperative aftercare

Postoperative aftercare is identical to nonoperative treatment with 6 weeks of non-weight-bearing cast-immobilization and 4 weeks of walking boot. Stitches are removed, and cast changed at 2-week visit. The cast and K-wires stabilizing the TMT IV and/or V joints are removed at 6-week visit. Thrombosis prophylaxis and analgesic medication is planned individually.

### Follow-up

All follow-up visits will be conducted in the trauma outpatient clinic of the hospital where the patient was primarily treated (Table 1). The visits are at 6 weeks, 10 weeks, 6 months, 12 months and 24 months after the injury. Standing x-ray of the injured foot and VAS score is obtained during every visit. AOFAS and VAS Foot and Ankle questionnaires will be completed during the 6, 12 and 24-month visits.

**Table 1 Tab1:** Assessments and procedures of the trial

	Medical history	Radiograph	CT	VAS	AOFAS	VAS FA
Baseline	X	X	X			
6 weeks		X		X		
10 weeks		X		X		
4 months		X		X		
6 months		X		X	X	X
1 year		X		X	X	X
2 years		X		X	X	X

### Power analysis

In this trial, the widely recognized AOFAS will be used as the main outcome measure. The clinically significant difference in AOFAS has been reported to be 8.36 (SD 11.16) points [56]. Assuming a 10-point difference in the AOFAS score and a standard deviation of 12 points, the estimated sample size is 23 patients (delta = 10, sd = 12, alpha = 0.05, power 0.8). We will assume a 20% drop-out rate in both groups, and therefore the total patient count needed for both stratums will be 56 patients. Due to block randomization in blocks of ten, 60 patients will be recruited.

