### Statistical analysis

The baseline characteristics will be reported as mean (standard deviation), median (quartiles) or proportion. Study groups will be compared using t-test, Mann-Whitney U or Fisher’s exact test. Primary (AOFAS) and secondary outcomes (VAS-FA, VAS, complications, secondary surgery) will be compared at 12 months and 24 months using the Mann-Whitney U test. The results will be presented with 95% confidence intervals, and therefore a *p*-value of < 0.05 will be considered statistically significant. The data will be analyzed according to the intention-to-treat principle, assuming the patients change group during the study. The statistical analysis will be performed with SPSS© version 22.

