### Time schedule

The recruitment of patients started in 2011 and it will be continued until the number of patients achieves the estimated volume of power analysis. The final results will be analyzed after the 2-year follow-up period of the last recruited patient. In October 2017, 51 patients had been included in the study. The final report will be published by the end of 2021.

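### The 20% drop-out allowance is multiplied on rather than divided out, so 56 should be 58; the planned 60 covers this slip but gives about 78% power, not 80%, with the planned Mann-Whitney test

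*Protocol article*

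**What the plan says.** The Power analysis section of the protocol article starts from the inputs "Assuming a 10-point difference in the AOFAS score and a standard deviation of 12 points" and reports that "the estimated sample size is 23 patients", with the settings "delta = 10, sd = 12, alpha = 0.05, power 0.8". It does not name the test or formula used. It then allows for losses: "We will assume a 20% drop-out rate in both groups, and therefore the total patient count needed for both stratums will be 56 patients". The following sentence raises the number to be recruited to 60 and gives the randomisation block size of ten as the only reason.

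The Statistical analysis section says that the primary outcome (AOFAS) and the secondary outcomes "will be compared at 12 months and 24 months using the Mann-Whitney U test". The Time schedule section says of recruitment that "it will be continued until the number of patients achieves the estimated volume of power analysis", without repeating a number.

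**The concern.** An allowance for drop-out should return the required number of completers once the assumed losses have occurred. Adding 20% does not do this, because the 20% loss applies to the larger, inflated number. The stated total of 56 therefore fails the protocol's own requirement of 23 per arm at the protocol's own drop-out rate.

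Two further points run the same way. The 23 matches a formula that ignores estimation of the SD, and the primary comparison is planned with a rank test, which under normal scores needs slightly more patients than a t-test. At stake is whether the stated 80% power describes the trial as it will be run and analysed, and whether any later re-planning that starts from 23 and the factor 1.2 would repeat the shortfall.

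**Working it through.** **Inputs.** From the Power analysis section: difference 10 points, SD 12, alpha 0.05, power 0.80, drop-out 20% in both groups. From the Statistical analysis section: Mann-Whitney U test. Three assumptions are needed:

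- Alpha is two-sided. The article does not say so, but two-sided alpha reproduces 23, one-sided gives 18–19, and it fits the statement "The results will be presented with 95% confidence intervals".
- Allocation is 1:1 within the blocks of ten.
- The total of 56 or 60 serves one two-arm comparison.

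**Reproducing the stated figures.**

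- Normal approximation: n per arm = 2 × (1.960 + 0.842)² × (12/10)² = 22.6, rounded up to 23. This is the stated figure, and it is per arm.
- Drop-out: 23 × 1.2 = 27.6, so 28 per arm and 56 in total. This is also the stated figure.

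**Checking the drop-out step.**

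- Completers from 28 per arm: 28 × 0.8 = 22.4, below 23.
- Correct inflation: 23 / (1 − 0.20) = 28.75, so 29 per arm and 58 in total.
- Cost of this slip alone, on the normal approximation: 79.6% power at 22.4 per arm against 80.7% at 23, about one point.

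**Requirement by test.**

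| Basis | Completers per arm | Randomised in total |
|---|---|---|
| Normal approximation | 22.6, so 23 | 23/0.8 = 28.75, so 58 |
| Two-sample t-test (noncentral t) | 23.6, so 24 | 24/0.8 = 30, so 60 |
| Mann-Whitney, normal scores (efficiency 3/π = 0.955) | 23.6/0.955 = 24.7, so about 25 | 62 to 64 |

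The range in the last row is a matter of rounding: 24.7/0.8 = 30.9 gives 31 per arm, or 62. Rounding to 25 first gives 25/0.8 = 31.25, so 32 per arm, or 64.

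**Power after 20% loss.**

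| Randomised | Completers per arm | t-test | Mann-Whitney |
|---|---|---|---|
| 56 | 22.4 | 77.8% | about 76% by efficiency (about 75% at 22 per arm) |
| 60 | 60 × 0.8 / 2 = 24 | 80.7% | 78.8% by efficiency, 78.1% by simulation |

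The simulation used 40,000 trials with normal scores. At 25 completers per arm it gave 79.7% to 80.2% for the Mann-Whitney test, depending on the continuity correction. Rounding scores to whole points and capping them at 100, with assumed means of 78 and 88, left the result at 24 per arm at about 78%.

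**The case against.** The strongest reply is that 56 is only an intermediate figure. The next sentence of the same section sets recruitment at 60, which covers the corrected drop-out figure (58) and equals the t-test requirement (60). This stands. A reader who stops at 56 might infer that the trial is planned at about 75% power, but that figure describes 22 completers per arm, and the plan recruits 60.

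Two other inferences are tempting and not supported:

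- That a t-test figure of 23.6 was rounded down to 23. The normal approximation, 22.6 rounded up, matches exactly; truncation is only one possible reading, and the article does not say which formula was used.
- That the Time schedule section ends recruitment at 56. It refers back to the power analysis, and that section ends at 60. The two sections do not contradict each other, although naming the number would remove doubt.

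It can also be said that sizing on means and analysing by ranks is common practice, and that a gap of about two points is small beside the uncertainty in the inputs. At 24 per arm, t-test power moves from 83.9% to 77.4% as the SD goes from 11.5 to 12.5. That is fair and is why the point is minor. It does not make 56 the correct result of the stated inputs, and the extra four patients are attributed to block size rather than to the losses they in fact cover.

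**Conclusion.** Minor, and wrong as written. On the protocol's own inputs the total after drop-out is 58, not 56. The planned 60 absorbs both this slip and the move from the normal approximation to the t-test. What remains is a shortfall of about two points against the stated 80%, and it comes from the choice of the Mann-Whitney test rather than from the drop-out arithmetic.

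The conclusion rests on two-sided alpha, 1:1 allocation, roughly normal scores with SD 12, exactly 20% loss, and the reading of 60 as one two-arm comparison. The last assumption matters most. The article speaks of the count for both strata together and does not make clear whether 60 is per stratum or overall. If 60 had to serve both strata equally, there would be 15 per arm and 12 after losses, with t-test power of about 50%. That is a separate question and much larger than the one settled here.

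**What to change.** In the Power analysis section:

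- Replace 56 with 58, obtained as 23/0.8 = 28.75, so 29 per arm. Alternatively, restate the basis as a t-test with 24 completers per arm and give 60.
- Name the test or formula behind the calculation, and state that alpha is two-sided and allocation 1:1, if that is what was intended.
- State that 60 randomised, with 20% drop-out, gives about 81% power with a t-test and about 78% with the planned Mann-Whitney test, for one two-arm comparison.

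In the Time schedule section, name 60 as the recruitment number so that both sections give the same figure.

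The cost is a few words in two sections. No extra enrolment is needed, and neither the primary outcome nor the planned test has to change.

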### Hypotheses

Our primary hypotheses in the study are the following:i)The hypothesis of stratum I is that nonoperative treatment of non-dislocated Lisfranc injuries yields better outcome in terms of AOFAS, VAS and VAS-FA score compared with operative treatment (ORIF).ii)The hypothesis of stratum II is that PA of dislocated Lisfranc injuries yields better functional outcome in terms of AOFAS, VAS and VAS-FA score compared with ORIF, and PA results in fewer secondary operations than ORIF.

The results of both strata will be analyzed and reported separately.

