## Discussion

This publication presents a prospective, randomized, national multi-center trial. It gives details of patient flow, randomization, aftercare and methods of analysis of the material and ways to present and publish the results. The limitations of this study are limited patient blinding due to the nature of the treatment (operative versus nonoperative) and using a primary outcome measure (AOFAS) that has not been validated in Finnish. The strength of this study is that this is the first study to compare the nonoperative and operative treatment of Lisfranc joint injuries in a prospective and randomized study setting with an adequate number of patients. As the previous literature provides only two contradictory randomized controlled trials on this matter, the benefits of this study are to provide evidence-based knowledge on the treatment of these injuries.

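### The target of 56 (60 recruited) is the size of one two-arm comparison but is stated for both strata together; read as written, 80% power is not delivered in both strata, and an even split gives about 50% in each

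*Protocol article*

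**What the plan says.** The Power analysis section names the AOFAS as the main outcome and gives the calculation: "Assuming a 10-point difference in the AOFAS score and a standard deviation of 12 points, the estimated sample size is 23 patients", with the inputs listed as "delta = 10, sd = 12, alpha = 0.05, power 0.8". It does not say whether 23 is per arm or in total. After a 20% allowance for drop-out it concludes that "the total patient count needed for both stratums will be 56 patients", and then: "Due to block randomization in blocks of ten, 60 patients will be recruited".

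The Randomization section randomises each injury type separately: non-dislocated injuries to nonoperative treatment or ORIF, dislocated injuries to ORIF or PA. The Hypotheses section adds: "The results of both strata will be analyzed and reported separately". The Statistical analysis section compares the AOFAS with the Mann-Whitney U test.

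The Time schedule section says that recruitment began in 2011 and runs until the number from the power analysis is reached. It gives one study-wide count, "In October 2017, 51 patients had been included in the study", and a final report by the end of 2021, after two years of follow-up of the last patient. The Discussion describes the trial as one "with an adequate number of patients".

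**The concern.** The design has four arms in two comparisons that share no patients and are never pooled. A sample size for one comparison cannot serve as the total for both. If it does, each stratum has about half the patients that the calculation calls for, and the 80% in the text describes a trial of a different size.

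The primary endpoint is affected in both strata. At roughly even odds of detecting the assumed 10-point difference, a non-significant result says little. The risk is sharpest in stratum I, where the Abstract frames the hypothesis as a similar outcome: a wide, non-significant comparison could be taken as support for similarity. The Discussion's statement about adequate numbers would encourage that.

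**Working it through.** **Inputs.** Power analysis: difference 10, SD 12, alpha 0.05, power 0.8, drop-out 20%, totals 56 and 60. Randomization and Hypotheses: two separate two-arm comparisons. Time schedule: 51 patients by October 2017, start in 2011. Ethics: approval on 11 November 2011. Assumed here because not stated: 1:1 allocation and a two-sided alpha. Two-sided reproduces the article's 23; one-sided gives 18.

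**1. Reproducing 23.** n per arm = 2 × [(1.960 + 0.842) × 12 / 10]² = 22.6, so 23. The t-test calculation gives 23.6, so 24. The stated 23 is therefore the number per arm.

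**2. Reproducing 56.** 2 arms × 23 = 46, and 46 × 1.2 = 55.2, rounded up to 56 (or 28 per arm × 2). So 56 is the total for one two-arm comparison.

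**3. If 60 is the overall target, split evenly.** 60 / 2 = 30 per stratum, or 15 per arm. After 20% drop-out, 15 × 0.8 = 12 per arm. Power for a 10-point difference with SD 12, by noncentral t and by Mann-Whitney simulation (normal data, 20,000 runs):

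| Evaluable per arm | Scenario | t-test | Mann-Whitney |
|---|---|---|---|
| 12 | 60 overall, even split, 20% drop-out | 0.50 | 0.46 |
| 15 | 60 overall, even split, no drop-out | 0.60 | 0.56 |
| 24 | 60 per stratum, 20% drop-out | 0.81 | 0.78 |

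**4. Uneven split.** With 40 and 20 recruited, 32 and 16 are evaluable, that is 16 and 8 per arm. T-test power is 0.63 and 0.34.

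**5. Can any split give both strata 80%?** Each stratum needs 2 × 23 = 46 evaluable patients (48 by the t-test), so both need 92 (96). Sixty recruited supply 48 after drop-out, and 60 with none. No split works.

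**6. Detectable difference and precision at 12 per arm.** The difference detectable with 80% power (t-test) is 14.4 points, against the assumed 10. The standard error of the difference is 12 × √(2/12) = 4.90. With t(22) = 2.07, the 95% CI half-width is about 10.2 points.

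**7. Which reading fits the schedule?** From the ethics approval to October 2017 is about 5.9 years, so 51 / 5.9 = 8.6 patients per year. Reaching 60 takes 9 more, about 1.0 year, to late 2018; two-year follow-up then ends in late 2020. Reaching 120 (60 per stratum) takes 69 more, about 8.0 years, to about 2025, before any follow-up.

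**Side note on drop-out.** For one comparison, dividing by 0.8 gives 46 / 0.8 = 57.5, so 58 rather than 56. Recruiting 60 absorbs this, since 60 × 0.8 = 48, or 24 per arm.

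**The case against.** The strongest reply is that 56 was meant for each stratum. The number is exactly the size of one two-arm comparison, and the drop-out sentence speaks of two groups, not four. On that reading 60 per stratum leaves 24 evaluable per arm, t-test power is 0.81, and the calculation is sound. This reading is possible, so a flat statement that each stratum has 50% power would go too far. It does not clear the text, however: the sentence gives a total for both strata, nothing says per stratum or each, and the report date would then be out of reach at the observed rate.

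Further limits on what can be claimed:

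- About 50% assumes an even split. The article fixes no split, and 40/20 gives 0.63 and 0.34.
- A reader might infer that the timetable proves a target of 60 overall. It is strong circumstantial evidence only. The article says just that recruitment began in 2011, the projection assumes constant accrual, and a planned report date may be optimistic.
- A reader might infer that recruitment stops on the pooled count. The Time schedule section does not say whether the count is pooled or per stratum.
- A reader might treat the drop-out inflation as a second error of weight. It is not: rounding to 60 covers it for one comparison, and changing 56 to 58 in a sentence about both strata would leave the main error in place.

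**Conclusion.** The point stands in conditional form. The Power analysis section states a one-comparison sample size as the total for two separately analysed comparisons, so it needs correcting on either reading.

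Read as written, with 60 overall, the stated 80% is not delivered in both strata under any split. Under an even split, 1:1 allocation, two-sided alpha of 0.05 and the article's own 20% drop-out, power per stratum is about one half. Even with no drop-out it is only about 0.60 by t-test. This is the more natural reading of the words and the one that best fits the enrolment count and the report date.

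Read as 60 per stratum, the power claim holds by t-test (0.81), and the errors are instead the sentence on the total and the time schedule.

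The documents do not settle which was intended. They therefore do not support saying without qualification that every stratum has 50% power.

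**What to change.** 1. In Power analysis, state for each of 23, 56 and 60 whether it is per arm, per stratum or overall.
2. If 60 is the overall target, replace the 80% with what each stratum delivers, showing the assumed split. For an even split with 20% drop-out: power about 0.50 by t-test and 0.46 by Mann-Whitney for 10 points, detectable difference about 14.4 points, expected 95% CI half-width about 10 points. Remove the Discussion's claim of adequate numbers.
3. If 60 per stratum was meant, say so in Power analysis and correct the Time schedule to match the accrual rate.
4. In Time schedule, state whether recruitment closes on per-stratum or overall counts.

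Cost: if 60 is the overall target, these are wording changes. No extra patients are needed, but the stated power becomes less favourable. If 60 per stratum was meant, the corrected schedule is much longer. Enlarging a trial planned at 60 overall to 60 per stratum would double it; that is a separate decision for the sponsor and is not needed to correct the text.

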### Statistical analysis

The baseline characteristics will be reported as mean (standard deviation), median (quartiles) or proportion. Study groups will be compared using t-test, Mann-Whitney U or Fisher’s exact test. Primary (AOFAS) and secondary outcomes (VAS-FA, VAS, complications, secondary surgery) will be compared at 12 months and 24 months using the Mann-Whitney U test. The results will be presented with 95% confidence intervals, and therefore a *p*-value of < 0.05 will be considered statistically significant. The data will be analyzed according to the intention-to-treat principle, assuming the patients change group during the study. The statistical analysis will be performed with SPSS© version 22.

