**Methods:**

This study is a prospective, randomized, national multi-center trial. The trial comprises two strata: Stratum I compares cast-immobilization versus open reduction and internal fixation (ORIF) treatment of non-dislocated Lisfranc joint injuries. Stratum II compares PA versus ORIF in the treatment of dislocated injuries of the Lisfranc joint. The main hypothesis of stratum I is that the nonoperative treatment of non-dislocated Lisfranc injuries achieves a similar outcome compared with operative treatment (ORIF). The hypothesis of stratum II is that PA of dislocated Lisfranc injuries yields a similar functional outcome compared with ORIF, but that PA results in fewer secondary operations than ORIF. The main outcome measure is the American Orthopaedic Foot and Ankle Society (AOFAS) Midfoot score and the secondary outcome measures are Visual-Analogue-Scale Foot and Ankle (VAS-FA), Visual-Analogue-Scale (VAS), rate of secondary operations and other treatment-related complications. The results will be analyzed after the 2-year follow-up period.

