There have only been two previous prospective randomized studies on ORIF vs PA. Ly and Coetzee [30] randomly assigned 41 patients with ligamentous Lisfranc injuries to either an ORIF group or a PA group. The PA group had a slightly better functional outcome (AOFAS score 88 vs. 69), a higher return to preinjury activity level (92% vs. 65%), a lower rate of revision surgery and less pain in the final follow-up. Implant removal due to prominent or painful screws was performed on 16 of the 20 patients in the ORIF group and on 4 of the 21 patients in the PA group. The implant removal was only performed due to painful hardware, on average at 6.5 months (range: from five to ten months). Follow-up radiographs showed loss of correction, increasing deformity, and degenerative joint disease in 15 of the 20 patients in the ORIF group and 7 of them required conversion to an arthrodesis. In the PA group, one patient had delayed union at seventeen weeks and one patient required a revision arthrodesis with bone graft. One patient suffered from a post-traumatic intrinsic compartment syndrome that resulted in claw toes. In the study by Henning et al. [33], 40 patients with acute Lisfranc joint fractures or fracture dislocations were randomized to primary ORIF or PA. A total of 8 patients dropped out before 3-months follow-up. There was a significantly higher rate of secondary surgery in the ORIF group. Statistically significant differences were not found in physical functioning with regard to SF-36 or SMFA scores at any follow-up time interval. In their systematic review and meta-analysis, Smith et al. [34] concluded that ORIF has a higher risk of implant removal compared with PA (risk ratio 0.23 (0.11–0.45) *p* < 0.001), although there were no statistically significant differences in revision surgery, PROMs or non-anatomic alignment. Cochran et al. [32] organized a retrospective comparative cohort study on PA versus ORIF in young athletic military personnel with low-energy Lisfranc injury. In their study, PA resulted in a faster return to military service, a lower implant removal rate and better fitness scores after 1 year.

In conclusion, PA seems to result in less secondary surgery, less implant removal and a faster return to activity. There is some evidence of a better functional outcome after arthrodesis, but the result is still controversial. Nevertheless, the current overall evidence slightly favors arthrodesis as a primary treatment of dislocated Lisfranc injuries.

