## Methods/design

The study is a prospective, randomized, national multicenter trial. The trial centers are Tampere University Hospital and Seinäjoki Central Hospital. The trial has been designed to compare the nonoperative and operative treatment of Lisfranc injuries. The trial includes two strata: Stratum I compares nonoperative treatment and operative treatment with ORIF for non-dislocated Lisfranc injuries. Stratum II compares ORIF and PA in dislocated Lisfranc injuries.

The primary outcome in this study is the AOFAS [54] measured after 6, 12 and 24 months. The secondary measured outcomes after 6, 12 and 24 months are VAS [55], VAS-FA [52], number of secondary operations (implant removal, secondary arthrodesis) and number of other treatment-related complications.

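### Secondary operations accumulate over follow-up, but they are compared at 12 and 24 months with a rank test that cannot use partial follow-up; a cumulative-incidence comparison with record-based ascertainment would

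*Protocol article*

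**What the plan says.** - **Endpoint.** Methods/design lists as a secondary outcome, after 6, 12 and 24 months, the "number of secondary operations (implant removal, secondary arthrodesis) and number of other treatment-related complications". The abstract calls it the "rate of secondary operations and other treatment-related complications".
- **Role.** The Hypotheses section puts it among the primary hypotheses of stratum II: "PA results in fewer secondary operations than ORIF".
- **Analysis.** The Statistical analysis section handles it in the same sentence as the questionnaire scores: "secondary outcomes (VAS-FA, VAS, complications, secondary surgery) will be compared at 12 months and 24 months using the Mann-Whitney U test".
- **Drop-out.** The Power analysis section says "We will assume a 20% drop-out rate in both groups". It gives no timing, and the figure serves only to enlarge the AOFAS sample size.
- **Analysis principle.** "The data will be analyzed according to the intention-to-treat principle, assuming the patients change group during the study". This explains intention-to-treat by change of group and does not address patients whose follow-up is incomplete.
- **Follow-up.** Patients are seen at the hospital that first treated them. Table 1 has no column for secondary operations.

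**The concern.** A questionnaire score at 24 months exists only if the patient completes it then. An operation count differs: each operation happens on a date, stays known once recorded, and the count is complete only when the whole period has been observed. A patient who has a screw removed at 7 months and then stops attending has a known operation but no complete 24-month count. A patient lost at 3 months has a count of zero but was not observed when implant removal tends to happen.

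The Mann-Whitney test needs one number per patient and has no place for length of follow-up. Run only on what was collected, it leaves two choices: omit both patients, or rank their partial counts as if complete. At stake is the precision, and in some settings the size, of a comparison named in the stratum II hypothesis. The point is confined to secondary surgery. It does not concern missing AOFAS scores or whether a rank test suits binary data.

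**Working it through.** **The plan's own figures.** There is no sample size or power for secondary operations. The AOFAS figure reproduces: n per group = 2 × (1.96 + 0.84)² × 12² / 10² = 22.6, so 23. Then 23 × 1.2 = 27.6, so 28 per group and 56 in total. The 20% enters the plan only here.

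**Inputs for the illustration**
- Implant removal in the earlier randomised trial of ligamentous injuries (Previous studies): ORIF 16/20 = 80%, PA 4/21 = 19%. The difference is 61 points.
- Timing of removal in that trial: 5 to 10 months, mean 6.5. Spread evenly over 5 to 10 months here (assumption).
- Drop-out: 20% per arm (Power analysis), unrelated to outcome (assumption).
- Timing of drop-out: not given, so three cases are shown. Early loss has a precedent in the other cited randomised trial, of 40 patients: "A total of 8 patients dropped out before 3-months follow-up".
- 30 patients per arm (assumption; the Power analysis wording is ambiguous).

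**Partial counts used as complete.** Apparent rate = true rate × (1 − 0.20 × share of drop-outs who leave before their operation would occur).
- All leave before 3 months: share 1, factor 0.80. Rates read 64% v 15%, difference 49 points.
- Leaving spread evenly over 0 to 24 months: share 7.5/24 = 0.3125, factor 0.9375. Rates read 75% v 18%, difference 57 points.
- All leave at 12 to 24 months: share 0, factor 1. Difference 61 points.

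**Part-followed patients omitted.** The difference stays at 61 points in all three cases. The cost is known operations thrown away. With 30 × (0.80 + 0.19) = 29.7 operated patients expected, simulation discards about 0, 4 and 6 of them in the three cases.

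**Censored 24-month cumulative incidence.** In simulation it is unbiased in all three cases. It is at least as precise as completers only: with evenly spread drop-out, the SD of the estimated difference is 0.104 against 0.113.

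**When bias can arise (assumed inputs)**
- True rate 50% in both arms, drop-out 30% v 10% before any operation, partial counts used: 0.5 × 0.7 = 35% v 0.5 × 0.9 = 45%, a false 10-point difference.
- True rate 50%, 10% of operated and 30% of unoperated patients leave, completers only: 0.45/(0.45 + 0.35) = 56%. Reversed: 0.35/(0.35 + 0.45) = 44%.

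**Power.** All drop-out is taken as early. Columns: operations fully known / completers only / drop-outs counted as zero.

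| Per arm, ORIF v PA rate | Fisher's exact test | Mann-Whitney on 0/1 outcome |
|---|---|---|
| 15, 80% v 19% | 89 / 83 / 67% | 95 / 92 / 80% |
| 30, 80% v 19% | 99.9 / 99.3 / 96.9% | 99.9 / 99.7 / 98.4% |
| 30, 60% v 19% | 87 / 79 / 72% | not computed |

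The Mann-Whitney figures use the asymptotic test with tie correction and no continuity correction. The 15 per arm (60 patients split over four arms) and the 60% rate are assumptions.

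**The case against.** A reader might infer that the trial will discard observed operations or score drop-outs as operation-free. The article says neither. It does not say that operations are captured only at visits, and patients are followed where they were treated. If operations were retrieved to 24 months for everyone, the planned comparison of counts would face no drop-out problem. This stands, and it makes the harm conditional.

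A reader might also treat the missing counting rule as the fault. It is not one: a journal article commonly leaves such a rule to the full protocol or analysis plan. What remains is the method the article does fix, namely test, time points and endpoint.

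A third tempting reading is that the difference will be understated by 12 points (61 to 49). That needs every drop-out to leave before operations begin, and then no observed implant removal is discarded by a completers analysis. The two harms belong to different timings, and the 20% is a planning allowance with no timing. With the cited rates and 30 per arm, the loss of power nearly vanishes.

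Finally, a count at a fixed horizon is a legitimate endpoint, and time to first operation alone would drop repeat operations, such as an arthrodesis after a screw removal. This is right and is built into the fix.

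**Conclusion.** The point holds as a cheap improvement of minor to moderate weight. The article fixes, for an accumulating event in the stratum II hypothesis, a comparison that cannot use partial follow-up, while allowing for 20% drop-out. Unless operations are retrieved or imputed, omitting part-followed patients loses precision and is biased only if leaving depends on surgery. Using partial counts turns an illustrative 61 points into 49 to 61, depending on when patients leave.

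These sizes rest on implant-removal rates and timing from one cited trial and on drop-out that is equal between arms and unrelated to outcome. They do not cover later secondary arthrodesis, whose timing the article does not give. The power figures are illustrations under assumed arm sizes and rates.

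The documents do not show that the planned result will be biased.

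**What to change.** In the Statistical analysis section, take secondary surgery out of the sentence on 12- and 24-month Mann-Whitney comparisons and state that:

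1. Secondary operations on the study foot up to 24 months are ascertained for every randomised patient, attending or not, from the records of the two trial hospitals.
2. The arms are compared on the 24-month cumulative incidence of a first secondary operation, with untraced patients censored at last contact, reporting the difference and its 95% confidence interval.
3. The total number and type of operations per arm are reported as a descriptive count, so that repeat operations are kept.

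The cost is a short change of text and a record check for about 12 patients (20% of 60). Operations at other hospitals may be missed. Censoring at last contact still assumes that leaving is unrelated to later surgery, but an operation seen before a patient leaves is kept.
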